
#### 2.8.2. Safety evaluation analysis

Safety evaluation variables, including clinical laboratory test results, will be presented descriptively. However, significantly abnormal test results may be described individually if necessary.

##### 2.8.2.1. Adverse events

All adverse events occurring in this clinical study will be standardized by system organ class (SOC) and preferred term (PT) based on the MedDRA dictionary. For adverse events and adverse drug events occurring in clinical research trials, the frequency (number of subjects), percentage, and number of occurrences are presented based on the SOC and PT according to the CP applied and CP non-applied groups. For adverse reactions that occurred by severity, Based on SOC and PT, the frequency of occurrence (number of subjects), percentage, and number of occurrences are presented.

For serious adverse reactions, the frequency (number of subjects), percentage, and number of occurrences will be presented based on the SOC and PT according to the CP applied and CP non-applied groups. The adverse reactions, duration, course, severity, outcome, and causal relationships will be summarized in a list. In addition, individual lists of all subjects with adverse events will be presented, including the group, reported adverse events, start date/time and end date/time, course, severity, seriousness and relationship, actions taken, and final outcome. Adverse events leading to discontinuation of the study will be listed separately. The adverse events will be summarized based on the preferred terms according to MedDRA.

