## 2. Materials and methods

### 2.1. Study design

This single-center prospective observational study will be performed at Kyung Hee University Medicine Hospital and Kyung Hee University Korean Medicine Hospital to analyze the effectiveness, economy, and safety of using an integrated medical service CP in patients with L-HNP. The patients will be divided into groups that apply critical pathway of integrative medical services and those who do not.

From among the patients who agree to participate in the study, those who meet the inclusion criteria will be registered as research subjects. Among them, those who agree to participate in the integrated medical service CP will be assigned to the test group (integrated medical service CP applied group) and those who do not will be assigned to the control group (integrated medical service CP non-applied group). Both groups are further divided into a conservative treatment (CONS) group, an open discectomy (DISCEC) group, and an interbody fusion (FUSION) group based on the main medical treatment. In the test group, inpatient treatment will be administered according to the pathway of the prescribed protocol. In the control group, inpatient treatment will be administered based on the treating doctor’s judgment, without a prescribed pathway. The test group patients will be discharged after being hospitalized for a set hospitalization date, whereas in the control group, the time of discharge will be determined according to the judgment of the clinician. The study will be completed when the patients are evaluated during an outpatient visit to the Department of Neurosurgery of Kyung Hee Medical Center 4 weeks after discharge.

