##### 2.7.1.2. Secondary outcomes

For the CONS, DISCEC, and FUSION groups, we will evaluate whether the decrease in the VAS score of the CP group is statistically significant compared to that in the corresponding control group on day 1 of hospitalization and discharge.For the 3 treatment groups, we will evaluate whether the changes in the ODI, SF-36, and EQ-5D-3L scores in the CP group are statistically significant compared to those in the corresponding control group on day 1 of hospitalization and 4 weeks after discharge.For the 3 treatment groups, we will evaluate whether the changes in the ODI, SF-36, and EQ-5D-3L scores in the CP group are statistically significant compared to those in the corresponding control group on day 1 of admission and discharge.The average length of hospitalization will be compared between the CP group and the corresponding control group for all 3 treatment groups.After the patient is discharged from the hospital, a questionnaire for employee satisfaction will be used to evaluate the satisfaction of doctors, nurses, and hospital staff with the application of CP.After the patient is discharged from the hospital, the patient’s satisfaction with the medical services will be investigated through a questionnaire, and the satisfaction scores between the CP group and the corresponding control group will be compared.We will compare the consultation waiting time between the CP group and the corresponding control group.In addition to the fixed oral preparations and intravenous infusions, the amount of pro re nate (Pro Re Nate) analgesic used for pain will be investigated and compared between the CP group and the corresponding control group.The CP application rate and completion rate will be analyzed in the 3 groups.

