#### 2.7.3. Safety evaluation

##### 2.7.3.1. Adverse events

Adverse events will be determined based on the severity and causal relationship with the test drug, and the incidence rate of adverse events, incidence rate of adverse events that caused dropout, and expression rate of serious adverse events will be analyzed.

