##### 2.7.3.3. Vital signs (blood pressure, pulse, respiratory rate, and body temperature)

The vital signs will be evaluated 3 times a day at 8-hour intervals from admission.

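### Adverse-event observation time is length of stay plus about 4 weeks, and stay follows a different discharge rule in each arm, yet crude percentages and counts by arm are planned

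*Protocol article*

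**What the plan says.** All references are to the protocol article.

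- **Discharge, CP arm (2.1):** "The test group patients will be discharged after being hospitalized for a set hospitalization date". The number of days is in figures that are not shown.
- **Discharge, control arm (2.1):** "the time of discharge will be determined according to the judgment of the clinician".
- **End of study (2.1, repeated in 2.4):** the study is complete when patients are "evaluated during an outpatient visit to the Department of Neurosurgery of Kyung Hee Medical Center 4 weeks after discharge". The last contact is therefore tied to discharge and not to admission.
- **Length of stay as an outcome (2.7.1.2):** "The average length of hospitalization will be compared between the CP group and the corresponding control group for all 3 treatment groups".
- **Adverse-event outcome (2.7.3.1):** the "incidence rate of adverse events, incidence rate of adverse events that caused dropout, and expression rate of serious adverse events will be analyzed". No time base is given for these rates.
- **Adverse-event analysis (2.8.2.1):** the count of patients affected, then "percentage, and number of occurrences are presented based on the SOC and PT according to the CP applied and CP non-applied groups". The same three measures are planned by arm for serious adverse reactions. Individual listings carry the start and end date and time of each event.

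Section 2.8.2 makes the safety analysis descriptive. The Abstract and the Introduction name safety, with effectiveness and economic feasibility, as something to be compared between the arms.

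**The concern.** A percentage of patients with at least one event is comparable between arms only if both arms are observed for similar lengths of time. Here the length of observation depends on a discharge rule that differs by arm. The study also treats length of stay as something the pathway may change: it is a compared secondary outcome, and the Introduction describes a critical pathway as a means of containing cost within a fixed hospital stay. The plan cannot allow for an effect on stay in one analysis and rely on equal stay in another.

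If the pathway shortens stay, the CP arm will tend to show fewer patients with events and fewer occurrences because it was observed for fewer days. If the pathway lengthens stay, the opposite follows. In either case a reader of the by-arm table could take a difference in follow-up for a difference in safety, which is one of the three stated objectives.

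**Working it through.** **The plan's own figure.** The article gives no number for this point. The arm size follows from section 2.5.4: 17 per group in 3 groups per arm gives 3 × 17 = 51 per arm and 102 in total.

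**Inputs**

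- Observed time per patient: L + 28 days, where L is length of stay (2.1 and 2.4).
- L: not in the text. Assumed to be 7 days in one arm and 7, 10 or 14 days in the other.
- Hazard h of a first recorded event: not in the text. Assumed constant, equal in both arms, at 0.01 or 0.02 per day.
- Detection: assumed equally complete before and after discharge, so that only the length of observation differs.

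**Patients with at least one event.** P = 1 − exp(−h × (L + 28)).

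| L (days) | Observed days | P at h = 0.01 | P at h = 0.02 |
|---|---|---|---|
| 7 | 35 | 1 − exp(−0.35) = 29.5% | 1 − exp(−0.70) = 50.3% |
| 10 | 38 | 1 − exp(−0.38) = 31.6% | 1 − exp(−0.76) = 53.2% |
| 14 | 42 | 1 − exp(−0.42) = 34.3% | 1 − exp(−0.84) = 56.8% |

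Differences at equal daily risk:

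- 7 versus 7 days: 0 points.
- 7 versus 10 days: 2.1 points (h = 0.01) or 2.9 points (h = 0.02).
- 7 versus 14 days: 4.8 points (h = 0.01) or 6.5 points (h = 0.02).

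The sign follows whichever arm stays longer.

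**Occurrences.** With a constant rate, the expected count is proportional to observed days. The ratio is 38/35 = 1.09 for 7 versus 10 days and 42/35 = 1.20 for 7 versus 14 days, whatever the rate. At 0.01 per day and 51 patients, that is 0.01 × 51 × 35 = 17.9 occurrences against 0.01 × 51 × 42 = 21.4. Per 100 patient-days both arms show 1.0.

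**Common window.** Over the first 28 days from admission, P = 1 − exp(−28h) in both arms: 24.4% at h = 0.01 and 42.9% at h = 0.02. The difference is 0 whatever the stays. Everyone who attends the visit 4 weeks after discharge has been followed for at least 28 days from admission.

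**Scale against sampling error.** For 29.5% versus 34.3% with 51 per arm, the standard error is √(0.295 × 0.705/51 + 0.343 × 0.657/51) = 9.2 points. Over the scenarios in the table it is about 9 to 10 points.

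**The case against.** **The analysis is descriptive, and denominators belong in the SAP.** No between-arm test of adverse events is planned, counts and percentages by SOC and PT are the ordinary format, and a SAP that is not shown may add exposure-adjusted rates. The unspecified incidence rate in 2.7.3.1 does not rule them out. This lowers the weight of the point without removing it. Section 2.8.2.1 already fixes the by-arm measures for a stated comparative objective, and descriptive percentages by arm will be compared by readers.

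**Admission to 4 weeks after discharge is a legitimate whole-pathway period.** Stay is part of the pathway, and the primary outcome uses the same endpoint. That is a reason to keep the crude table, but it does not make that table a comparison of risk over equal time.

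**The size is assumed, and small against sampling error.** Both are true. The constant hazard matters too: with stays of 7 versus 14 days, the extra observation falls on days 36 to 42 from admission. If events cluster soon after admission or a procedure, the excess is smaller than the table shows. A larger sample would shrink the sampling error but would leave the systematic part in place.

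**A stronger reading that the text does not support.** A reader might infer that adverse events are looked for every 8 hours in hospital and only once afterwards, so that ascertainment falls sharply at discharge. The 8-hourly schedule in 2.7.3.3 reads "The vital signs will be evaluated 3 times a day at 8-hour intervals from admission"; it covers vital signs only. The article states no schedule for collecting adverse events in either period, its silence is not a finding, and the 4-week visit may collect events back to discharge. Closer watching in hospital is plausible but remains an inference.

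If detection did differ, a 28-day window would not cure it. Suppose recording is 0.01 per day after discharge and 5 times that in hospital, with stays of 7 versus 14 days:

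- Whole study: 1 − exp(−(0.35 + 0.28)) = 46.7% versus 1 − exp(−(0.70 + 0.28)) = 62.5%, a difference of 15.7 points before rounding.
- First 28 days: 1 − exp(−(0.35 + 0.21)) = 42.9% versus 1 − exp(−(0.70 + 0.14)) = 56.8%, a difference of 13.9 points before rounding.

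Most of such a bias would remain, so the point should not be argued, or its size quoted, on that basis.

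**Conclusion.** The point holds in this form: follow-up for adverse events is stay plus about 28 days, stay is governed by an arm-specific discharge rule and is itself under comparison, and the by-arm percentages and occurrence counts take no account of that.

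If stays differ, the longer-stay arm shows more events at the same daily risk. Under assumed stays of 7 versus 10 to 14 days, a constant hazard of 0.01 to 0.02 per day and equal detection, the effect is about 2 to 6.5 percentage points in patients with an event and 9% to 20% in occurrences. It is zero if stays are equal and smaller if events are concentrated early. The text does not allow the actual size or direction to be established. This is a modest, cheaply avoided weakness in how the safety comparison is presented; it does not show that the comparison is biased in a known direction.

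**What to change.** Change section 2.8.2.1 as follows:

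1. Base the CP-versus-control percentage of patients with an adverse event on a common window counted from admission that every completer covers, for example the first 28 days, using the recorded event start dates.
2. Report whole-study occurrences also per 100 patient-days by arm.
3. Keep the crude whole-study table as a descriptive summary.
4. Show a descriptive split at discharge, with two cautions stated beside it. The common window equalises total time but does not remove any difference between inpatient and outpatient detection. Inpatient rates may be distorted where an event itself prolongs the stay.

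No new data are needed: event start dates are already listed and length of stay is already an outcome. The cost is some wording and one or two extra tables. The downside is smaller counts per table, and events after the window are left out of the main percentage, though the crude table still shows them.

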**Methods::**

This single-center prospective observational study will be performed at Kyung Hee University Medicine Hospital and Kyung Hee University Korean Medicine Hospital. The inclusion criteria are a diagnosis of L-HNP on magnetic resonance imaging or computed tomography scans, age under 80 years, a visual analog scale score of 7 or higher for either lower back pain or lower extremity pain. The included 102 participants will be classified into 6 groups (n = 17 in each group): CP application with conservative treatment; CP application with open discectomy; CP application with intrabody fusion; conservative treatment without CP application; open discectomy without CP application; and interbody fusion without CP application. We will collect data on the visual analog scale, ODI, SF-36, and EQ-5D-3L scores; number of admission days; medical staff satisfaction; patients health service satisfaction; waiting time for consultations; use of pain relievers; and CP application and completion rates.

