### 2.4. Clinical trial plan and critical pathway schedule

Among patients with lumbar intervertebral disc herniation visiting the Neurosurgery outpatient department of Kyung Hee Medical Center, patients with a VAS score of 7 or higher who require hospitalization can consent to participate in this study. Following patient consent, the doctors and research nurses will screen the patients according to the inclusion and exclusion criteria, enroll those who pass the screening, and confirm the participants intention to receive treatment using an integrated medical service CP. Depending on their intention to participate in the CP application, participants will be classified into the test or control group. Upon admission, the patients will be assigned to the CONS group, DISCEC group, and FUSION groups according to the judgment of the medical staff. The test group will receive inpatient treatment according to a previously developed integrated medical service CP plan, and the control group will receive inpatient treatment according to the clinician’s judgment without a set protocol. The study will be deemed complete when all patients will be evaluated during an outpatient visit to the Neurosurgery Department of Kyung Hee Medical Center 4 weeks after discharge.

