### 2.8. Statistical analysis

#### 2.8.1. Efficacy evaluation analysis

##### 2.8.1.1. Primary outcome analysis

The primary outcomes will be analyzed based on the treatment groups. For each group, a normal distribution will be assumed for the difference in the VAS score measured on day 1 of hospitalization and at 4 weeks after discharge, and a *t* test will be performed. The means between the treatment groups (CP and control groups) will be compared. If normality is confirmed through the normality test for the VAS scores, the Mann–Whitney test will be performed.

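### Adverse-event tables pool nerve-block, discectomy and fusion patients within each arm, which dilutes harm confined to one treatment type and leaves the crude contrast open to surgical mix if the cells fill unequally (minor)

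*Protocol article*

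**What the plan says.** For adverse events and adverse drug events, section 2.8.2.1 states that frequencies, percentages and numbers of occurrences "are presented based on the SOC and PT according to the CP applied and CP non-applied groups". Serious adverse reactions are split by the same two arms, in a sentence that begins: "For serious adverse reactions, the frequency (number of subjects), percentage, and number of occurrences will be presented based on the SOC and PT according to". Neither sentence names CONS, DISCEC or FUSION. Subject-level listings are added: "individual lists of all subjects with adverse events will be presented, including the group, reported adverse events", without saying whether the group is one of two or one of six. Section 2.8.2 sets the general character of the analysis: "Safety evaluation variables, including clinical laboratory test results, will be presented descriptively".

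The rest of the article works by treatment type. Section 2.4.1 gives each type its own CP schedule. Section 2.7.1.1 compares the primary outcome between CP and the corresponding control within each type, and 2.8.1.1 follows: "The primary outcomes will be analyzed based on the treatment groups".

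On how the cells arise, the abstract plans equal sizes: "The included 102 participants will be classified into 6 groups (n = 17 in each group". Section 2.4 lets the patient decide the arm: "Depending on their intention to participate in the CP application, participants will be classified into the test or control group". Staff then decide the type: "Upon admission, the patients will be assigned to the CONS group, DISCEC group, and FUSION groups according to the judgment of the medical staff".

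**The concern.** A nerve block, an open discectomy and an interbody fusion carry different kinds and frequencies of adverse events, and the CP adds a different schedule to each. The article itself recognises a hazard specific to operated patients: section 2.6.2.1 calls for a check for hematoma before acupuncture near a surgical site, and CONS patients have no such site. A two-column table puts all these patients over one denominator.

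Two things are at stake, and safety is one of the study's three stated aims. First, an excess of harm in one type is divided by a denominator that includes the other two, and the table does not show where the events fell. This does not depend on how the cells fill. Second, if the arms end up with different proportions of block, discectomy and fusion patients, part of any crude difference between the arms reflects that mix and not the CP. This second effect arises only if the cells depart from plan.

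**Working it through.** **The plan's own figures.** Section 2.5.4 uses d = 1.15, SD = 1.12, two-sided 5% and 80% power:

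n = 2 × 1.12² × (0.8416 + 1.9600)² / 1.15² = 14.89, rounded up to 15 per group.

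Allowing for 10% dropout, 15 / 0.9 = 16.7, rounded up to 17. Over six groups, 6 × 17 = 102. The stated 15, 17 and 102 reproduce. Each arm is therefore planned as 17 CONS, 17 DISCEC and 17 FUSION, 51 in all.

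**Dilution at the planned cells.** The denominators come from the article; the event counts are illustrative.

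- Three affected patients, all in CP-FUSION: 3/17 = 17.6% in the cell, 3/51 = 5.9% in the pooled CP column.
- Four affected patients, all among operated CP patients: 4/34 = 11.8% among the operated, 4/51 = 7.8% pooled.

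When all events fall in one of three equal cells, the pooled percentage is one third of the cell percentage, whatever the count.

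**Effect of surgical mix.** The crude rate in an arm is Σ(nₖ × rₖ) / Σnₖ, where nₖ is the number of patients of type k and rₖ the event rate for that type. To isolate mix, rₖ is set equal in both arms, so there is no CP effect. The article gives no event rates. The assumed rates are 5% CONS, 15% DISCEC and 30% FUSION, with 2/10/20% and 5/20/40% as the range. Cell counts are in the order CONS/DISCEC/FUSION.

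| CP cells | Control cells | CP crude | Control crude | Difference (points) | Range over rate sets |
|---|---|---|---|---|---|
| 17/17/17 | 17/17/17 | 16.7% | 16.7% | 0.0 | 0.0 |
| 17/17/15 | 15/17/17 | 16.1% | 17.1% | 1.0 | 0.7 to 1.4 |
| 20/17/14 | 14/17/20 | 15.2% | 18.1% | 2.9 | 2.1 to 4.1 |
| 25/16/10 | 10/16/25 | 13.0% | 20.4% | 7.4 | 5.3 to 10.3 |

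The last row in full: CP (25 × 0.05 + 16 × 0.15 + 10 × 0.30) / 51 = 6.65/51 = 13.0%; control (10 × 0.05 + 16 × 0.15 + 25 × 0.30) / 51 = 10.40/51 = 20.4%. The standard error of that difference is √(0.130 × 0.870/51 + 0.204 × 0.796/51) = 7.4 points, so even a gross imbalance produces a shift of about one standard error.

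The second row keeps every cell at the required 15 or more. The third and fourth rows leave CP-FUSION at 14 and 10, below that minimum.

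**The case against.** A reader might infer that the plan as written makes a difference in surgical mix appear as a CP safety effect. The documents do not support that. Both arms are planned at 17/17/17, and at equal mix the spurious difference is exactly zero for any event rates. A shift of 5 to 10 points needs cells so far from plan that the primary comparison would already be short of patients. What stands is the possibility: the patient chooses the arm, staff choose the type, and the article describes no way of filling the cells to 17.

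A reader might also infer that events will be shown only by arm. The article does not say so, and the full protocol or SAP may add strata. The two-group wording could also be shorthand: section 2.8.1.2 describes length of stay, waiting time and as-needed analgesic use as CP versus control, although 2.7.1.2 compares each with the corresponding control group. For those outcomes, however, another section supplies the finer comparison. For adverse events neither 2.7.3.1 nor any other section does, so the two-group presentation is the choice the article states.

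Two further points carry some weight. Safety is descriptive and no test of adverse events between the arms is planned. But percentages in arm columns still invite a comparison. The tables also give raw counts, and the listings show each affected subject's group, so a cluster in a study of 102 patients might be noticed. But the listings cover only subjects with events, give no denominators, and do not say which grouping they use.

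**Conclusion.** The point holds in a limited form and is minor. The stated adverse-event and serious-adverse-reaction tables pool three treatment types that the article otherwise keeps apart. Dilution follows directly and does not depend on mix; at the planned cells it is a factor of three for harm confined to one type. Confounding by surgical mix is conditional: zero at the planned cells, about 1 point for a small imbalance and about 7 for a large one under the assumed rates of 5/15/30%. Those rates and the unequal cells are assumptions made for illustration and do not come from the documents.

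**What to change.** In section 2.8.2.1, present adverse events and serious adverse reactions for CP and control within each of CONS, DISCEC and FUSION, with the stratum denominators, alongside the overall CP and control columns. State that the group shown in the subject listings is one of the six.

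Add one conditional sentence: if an overall CP-versus-control safety statement is made and the cells are unequal, it will rest on a stratum-weighted difference (for example with Mantel-Haenszel weights) and not on the crude percentages. An interval for that difference is optional in a descriptive section. Weighting by type would remove the effect of surgical mix, but not confounding by patient choice within a type.

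The cost is a change to the table shells and a sentence or two of text. The six groups are already formed, so no new data are needed. The downside is sparser table cells, with about 17 patients behind each percentage.
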